### Data collection procedures

Patients will receive detailed written information on the aim of the study. After giving their written informed consent data will be collected by means of paper documents. For every patient a dossier with the different case report forms will be created. The forms are encoded; the code is stored at each primary care physicians’ practice. If a case-tracking is needed (in case of adverse events) it can be decoded. The transfer from paper to electronic data will be carried out through a research associate and controlled by a second research associate. Grouping of diagnoses and drugs will be organized by standardised databases.

### Statistical analysis

The primary data analysis will follow the intent-to-treat (ITT) approach. This means that all available data from all individuals will be analyzed according to treatment group assignment, regardless of whether or not each individual actually received the assigned treatment.

The primary outcome, change in the number of drugs 12 months after applying the deprescribing tool, will be compared by using a *t* test for independent groups comparison. Hierarchical regression will be used to consider the cluster-design for potential confounder. Determinants associated with a change of the medication are investigated by exploratory, multivariate regression analysis.

For secondary outcomes, parametric (*t* test) or non-parametric tests (chi-square and Wilcoxon test) will be used where appropriate.

Descriptive statistics will be used to describe the study population. Drop-out and loss to follow-up will be described.

In case of study discontinuation the collected data that are hitherto available will be anonymized and evaluated.

The last observation carried forward (LOCF) method will be used for dealing with the missing data for patients who have dropped out. The drop-out rate and the causes of drop-outs will be compared between the two groups to investigate the possible influence of the intervention. To estimate the last observation carried forward-effect a per-protocol (PP) analysis will be applied.

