### Recruitment and eligibility of primary care physicians

PCPs are eligible for participation if they provide care in the routine primary setting to unselected patients. About 1700 PCPs in the Canton of Zurich will be invited by a formal letter of the Institute of Primary Care of the University of Zurich.

PCPs who finally agree to participate will be listed in alphabetical order. If two PCPs of the same practice agree to participate, the first name in the alphabet receives a number which is valid also for the second one in order to avoid contamination between groups. Randomization will be stratified according to the practice size (e.g. single-handed versus group practice). The randomization scheme will be generated by using the website Randomization.com (http://www.randomization.com) and group assignment will be performed by a study nurse not involved in further data analysis. The PCPs with the corresponding numbers will be randomly allocated to the intervention and control group, respectively.

PCPs will be informed only after completion of the study about the group they have been randomized to (intervention or control group) in a debriefing session. At this time, an education session on how to use the algorithm will be offered to the control group.

If the number of the required 33 (see power calculation below) participating PCPs cannot be reached, the randomization will be done with the interested PCPs and the recruiting will be expanded to other Cantons of the northern area of Switzerland, followed by another randomization process.

Each PCP in the intervention and control groups will receive a financial allowance.

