### Primary outcomes measures

Change in the number of drugs (deprescribing rate) 12 months after applying the tool.

The primary outcome will be calculated on the basis of the medication list, provided by the practice nurse or the PCP at baseline (before the intervention) and 12 months afterwards.

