### Sample size calculation

Assuming a 0.05 2-sided significance level, 30 clusters (on PCP-level) including 13 patients each would have an 80 % power to detect a difference of 1 drug, which we consider to be clinically relevant.

Based on previous studies [14] we assumed an intracluster correlation coefficient (ICC) of 0.02 for the primary outcome and a standard deviation of 2.8 [21]. In consideration of a drop-out rate of 10 %, 33 PCPs (16 respectively 17 PCPs with 215 patients in each arm) are needed.

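### The t test named for the primary outcome uses neither the baseline drug count nor the randomisation stratum; adjusting for both gains precision at no data cost

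*Protocol article*

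**What the plan says.** All references are to the protocol article.

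- **Statistical analysis:** "The primary outcome, change in the number of drugs 12 months after applying the deprescribing tool, will be compared by using" an independent-groups t test. The next sentence adds: "Hierarchical regression will be used to consider the cluster-design for potential confounder". It lists no covariates and does not say whether this model or the t test gives the primary result.
- **Primary outcomes measures:** the outcome is computed from the medication list "provided by the practice nurse or the PCP at baseline (before the intervention) and 12 months afterwards". The baseline count therefore exists for every patient who contributes a change.
- **Recruitment and eligibility of primary care physicians:** "Randomization will be stratified according to the practice size (e.g. single-handed versus group practice"). If too few physicians join, those available are randomised and recruitment is widened, "followed by another randomization process".

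**The concern.** A t test on raw change has no term for the baseline count, the practice-size stratum or the randomisation wave.

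Subtracting the baseline fixes its coefficient at 1. When baseline and 12-month counts correlate at r with equal variances, the regression coefficient is r, so subtraction over-corrects by (1 − r). This has two effects. The estimate is noisier than it need be. In any one trial it also moves with whatever baseline difference chance has produced, and with about 15 clusters per arm such a difference is easy to get.

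The information that would remove both effects is already in the data. What is at stake is precision, and how far the reported figure in this one trial depends on the draw of practices. The validity of the randomised comparison is not at stake on this point.

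**Working it through.** **Inputs from the Sample size calculation section.** Two-sided 5% level, difference of 1 drug, 30 clusters of 13 (195 patients per arm), SD 2.8, ICC 0.02, stated power 80%. The text does not say whether 2.8 is the SD of the change or of the count. The correlation r is not given, so it is an assumption and a range is shown.

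**The plan's own figure.** Design effect = 1 + 12 × 0.02 = 1.24. SE of the difference = 2.8 × √(2 × 1.24 / 195) = 0.316. Power = Φ(1/0.316 − 1.96) = 88.6%, or 86.4% with a t reference on 28 df. The stated 80% is not reproduced: 80% power needs 123.07 × 1.24 = 152.6, so 153 per arm (306 in total). The stated size is larger than its inputs require.

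**Precision.** With equal variances, Var(adjusted)/Var(change) = (1 − r²)/(2(1 − r)) = (1 + r)/2. If 2.8 is the SD of the change, the unadjusted analysis, allowing for clustering, has 88.6% power and needs about 306 patients for 80%. With adjustment:

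| r | SE ratio √((1+r)/2) | Fall in SE | Power at 30 × 13 | Patients for 80% power, before drop-out |
|---|---|---|---|---|
| 0.5 | 0.866 | 13.4% | 95.5% | 230 |
| 0.7 | 0.922 | 7.8% | 93.0% | 260 |
| 0.9 | 0.975 | 2.5% | 90.1% | 290 |

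If 2.8 is instead the SD of the count, the SD of the change is 2.8√(2(1 − r)). Power without and with adjustment is then 76.3% and 91.3% at r = 0.3, 88.6% and 95.5% at r = 0.5, and 98.3% and 99.3% at r = 0.7.

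**Sensitivity to chance imbalance.** Take 2.8 and 0.02 as the SD and ICC of the baseline count (assumptions). The SE of the baseline difference is again 2.8 × √(2 × 1.24 / 195) = 0.316 drug. The shift in the estimate is (1 − r) × imbalance, in the direction opposite to the imbalance:

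| r | 1-SE imbalance (0.316) | 2-SE imbalance (0.632) |
|---|---|---|
| 0.5 | 0.16 | 0.32 |
| 0.7 | 0.09 | 0.19 |
| 0.9 | 0.03 | 0.06 |

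If 2.8 is the SD of the change, the count SD is 2.8/√(2(1 − r)). The 1-SE shift becomes 0.316 × √((1 − r)/2), which is 0.16, 0.12 and 0.07 drug at the same values of r.

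**Simulation check.** 4,000 trials at each r, with 30 clusters of 13, two strata of 16 and 14 practices allocated equally within stratum, and a true effect of −1. The adjusted estimate came from least squares on arm, baseline and stratum.

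| r | Mean change-score estimate | Its SD | SD of adjusted estimate | Slope on baseline difference: change score | Slope: adjusted |
|---|---|---|---|---|---|
| 0.5 | −0.99 | 0.318 | 0.277 | −0.49 | 0.01 |
| 0.7 | −1.00 | 0.244 | 0.225 | −0.30 | 0.01 |
| 0.9 | −1.00 | 0.141 | 0.138 | −0.09 | 0.01 |

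The change score is right on average, noisier, and dependent on the baseline difference as the formula says. The adjusted estimate is essentially free of that dependence.

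**Stratum.** With allocation balanced within strata, a stratum effect cancels from the difference between arms. A test that omits the stratum still leaves its variance in the estimated SE, so on this count the test tends to be conservative. The documents give no figure from which to size this.

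**The case against.** Four things can be said for the plan as written.

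1. **The hierarchical regression may carry these covariates, and a covariate list can be left to the full protocol or SAP.** The second half is fair: a missing list is no finding. A reader might infer that the plan ignores the stratum altogether, but the article does not support that. The omission is certain only for the t test. Even so, the t test is the method attached to the primary outcome, and the regression is not called primary.

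2. **The change score is a valid analysis of the outcome as defined.** This stands. A reader might infer that chance imbalance biases the estimate. It does not: over randomisations the estimate is centred on the true effect, provided enrolment does not differ by arm. What remains is an error conditional on the imbalance that happened. Regression to the mean after entry at five or more drugs acts in both arms under the same criterion, so by itself it does not bias the comparison either.

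3. **The gain may be small.** This also stands at high r: at r = 0.9 the SE falls by only 2.5%. If 2.8 is the SD of the change, an unadjusted analysis that allows for clustering already exceeds the stated 80% power. A reader might infer that the trial is underpowered without adjustment, and the documents do not show that.

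4. **The stratum and the second wave matter little.** Probably so. The wave is only a contingency, and omitting the stratum tends to be conservative.

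A larger matter in the same sentence is that a plain t test ignores clustering. At a design effect of 1.24 its two-sided type I error is 2(1 − Φ(1.96/√1.24)), about 7.8%. That is a separate point. Every SE comparison above applies the design effect to both analyses.

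**Conclusion.** The point holds as an improvement that costs nothing, not as an error that invalidates the primary analysis. The named t test discards a baseline count and a design factor that the trial already has, and the regression that might use them has no stated rank.

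Baseline adjustment is the main benefit: an SE lower by about 13% to 2.5% as r runs from 0.5 to 0.9, and removal of a conditional shift of 0.16 to 0.03 drug for a 1-SE baseline imbalance (twice that for 2 SE), against a target of 1 drug. These sizes rest on an assumed r and equal variances at the two times. The shifts also assume a baseline SD of 2.8 and an ICC of 0.02. Including the stratum aligns the analysis with the design but probably changes little.

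**What to change.** Make one hierarchical model the primary analysis. The outcome is the 12-month number of drugs. The fixed effects are arm, baseline number of drugs, practice-size stratum and, if a second randomisation is run, wave. Practice is a random effect. Report the adjusted mean difference with its confidence interval as the primary result. Keep the t test, if at all, only as a sensitivity analysis, and say so.

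The result is still a difference in number of drugs, so its interpretation does not change. The cost is a few lines of text and code; no new data are needed. The random practice effect also brings the clustering into the primary analysis.

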## Methods/Design

We will conduct a cluster-randomized controlled trial (randomization on PCP-practice level) with primary care physicians in the northern part of Switzerland (see Fig. 1). The design and methodology of our study is based on the experiences of a small pilot study.

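### The primary comparison is a t test with no allowance for practice clusters, and the hierarchical model that would allow for them is not made the deciding analysis

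*Protocol article*

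**What the plan says.** Methods/Design in the protocol article describes a "cluster-randomized controlled trial (randomization on PCP-practice level". The section on recruitment of physicians gives two physicians from one practice a shared number, so that they are allocated together, and stratifies the randomisation by practice size.

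The Sample size calculation takes the clustering into account: "we assumed an intracluster correlation coefficient (ICC) of 0.02 for the primary outcome and a standard deviation of 2.8".

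The Statistical analysis section first defines the intention-to-treat set at the level of the person: "all available data from all individuals will be analyzed according to treatment group assignment". It then says that the primary outcome will be compared by a t "test for independent groups comparison. Hierarchical regression will be used to consider the cluster-design for potential confounder". The second of these two sentences is the only mention of clustering in the analysis. For secondary outcomes the section lists the t test "or non-parametric tests (chi-square and Wilcoxon test) will be used where appropriate", with no reference to clusters.

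**The concern.** The plan assumes correlation within clusters when it sizes the trial, but names a test for the primary comparison that treats patients as independent. If patients of one practice resemble each other in how their drug counts change, an independent-groups t test on patients underestimates the variance of the difference between arms.

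The p value for the claim that the algorithm reduces drug numbers would then be too small and its confidence interval too narrow. The stated two-sided 0.05 level would not hold. The same applies to any secondary outcome compared between arms with these tests, such as drug counts at 6 months, quality of life or event rates.

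**Working it through.** **Inputs** (Sample size calculation):
- two-sided level 0.05
- 30 clusters of m = 13 patients, taken here as 15 clusters and 195 patients per arm (equal allocation is an assumption)
- ICC 0.02, SD 2.8, difference of 1 drug, stated power 80%
- after the drop-out allowance: 33 physicians and 215 patients per arm

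**1. The plan's own figure.** The design effect is DE = 1 + (13 − 1) × 0.02 = 1.24. The effective number per arm is 195 / 1.24 = 157.3. The correct standard error is 2.8 × √(2 / 157.3) = 0.316. Power is Φ(1 / 0.316 − 1.96) = Φ(1.21), about 88.6%, or 86.4% from a t distribution with 28 degrees of freedom. The stated 80% is therefore not reproduced. The mismatch is conservative and is a separate matter: the error computed below depends on cluster size and ICC, so spare power does not repair it.

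**2. Standard error of the patient-level t test.** It omits DE, so the ratio of its standard error to the correct one is 1 / √1.24 = 0.898. It is about 10% too small, and the interval is too narrow in the same proportion.

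**3. True two-sided error.** 2 × [1 − Φ(1.96 / √1.24)] = 2 × [1 − Φ(1.760)] = 0.078. A nominal 95% interval covers about 92%.

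**4. Simulation and range.** 40,000 trials per ICC value were simulated with no treatment effect, 15 against 15 clusters of 13. The ICCs of 0.05 and 0.10 do not appear in the protocol and only show how the error grows.

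| ICC | DE | SE ratio | Error, formula | Error, simulated (patients) | Error, simulated (cluster means) |
|---|---|---|---|---|---|
| 0.02 (protocol) | 1.24 | 0.898 | 7.8% | 7.7% | 4.9% |
| 0.05 (assumed) | 1.60 | 0.791 | 12.1% | 12.3% | 5.1% |
| 0.10 (assumed) | 2.20 | 0.674 | 18.6% | 18.5% | 5.0% |

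**5. Number analysed.** Because drop-outs are carried forward by LOCF, the test would run on about 2 × 215 = 430 patients, not 30 × 13 = 390. That is 430 / 33 = 13.0 per physician, so DE does not change. A practice contributing two physicians would form a larger cluster, which raises DE for that cluster if the ICC is the same.

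**The case against.** The strongest reply is that the plan does foresee a cluster-aware model. The hierarchical regression sentence follows directly on the t test, its English is unclear, and it could mean that the primary comparison is also fitted hierarchically. So a reader who infers that the protocol ignores clustering altogether goes too far. What remains is that the text attaches the comparison to the t test and the hierarchical model to confounders. Even on the generous reading, two analyses are named and the cluster-aware one is not said to decide.

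A second reply is that the unit of the t test is not stated, and a t test on practice means would be valid. That is correct. However, the section speaks of data from individuals and nothing points to practice means, so patient level is the natural reading, though an inference.

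Third, a reader might take an ICC of 0.05 as implied by the protocol, because power comes out at 79.6% (normal approximation) with that value. The protocol gives only 0.02 and the cause of the power mismatch is unknown. With 28 degrees of freedom the matching ICC would be about 0.04.

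Fourth, a reader might infer that every secondary outcome is affected to the same degree. The documents do not support this. Several items in Table 1, such as the reasons for change, the time the intervention takes and the perceived barriers, concern the algorithm or its encounter and may involve no test between arms. The ICC is given for the primary outcome only, so no error rate follows for quality of life or events. For the no-worsening hypothesis the effect has two sides: a plain difference test would declare harm too easily, while an interval that is too narrow would overstate how firmly harm is excluded.

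Deferring to an analysis plan that is not shown does not help, since the protocol itself names the test.

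**Conclusion.** The point holds and should be corrected before the data are analysed. As written, the primary outcome of a trial randomised by practice is compared by an independent-groups t test, and the hierarchical model is not the deciding analysis.

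On the protocol's own figures the true two-sided error is about 7.8% against the stated 5%, a moderate inflation. This rests on three conditions: the t test is run on patients, clusters are of equal size 13, and the ICC is 0.02. Larger ICCs make it worse, but the figures of about 12% and 19% are conditional on assumed values. For the secondary outcomes, the conclusion is only that those compared between arms need a method that respects the clusters. The size of the error there cannot be derived from the protocol.

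**What to change.** In the Statistical analysis section:
- Name the hierarchical model as the primary comparison. Specify a linear mixed model for the change in number of drugs at 12 months, or for the 12-month number adjusted for the baseline number. Include a treatment effect, the practice-size stratum, a random intercept for the randomised practice and small-sample degrees of freedom. Either form keeps the baseline count in the analysis, as the definition of the outcome requires.
- Drop the patient-level t test as the primary test. A t test on practice means can stand beside the model as a simple check.
- For secondary outcomes compared between arms (for example drug counts, quality of life, events), replace the unclustered tests with mixed models, GEE or cluster-level analyses.

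The cost is a few sentences and the analysis code. No further data or patients are needed, and the plan already mentions hierarchical regression.

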**Fig. 2 Fig2:**
[figure not shown]
Improving drug therapy in primary care (adapted from [20] and [21])

Indication of the drug in this patient (identifying undertreatment or overtreatment)Do the known possible adverse reactions of the drug outweigh the possible benefits? (Potential adverse events)Can the dosing rate be reduced with no significant risk? (Dosing problems)Is there another drug that may be superior to the one in question?

Finally, the result of this analysis will be discussed together with the patient. For each drug the PCP will note whether the patient agrees with the recommendation.

After obtaining informed consent from the patient, a practice nurse or the PCP creates a list of the patient’s present medication. Then, the PCP defines the four major clinical problems and, together with the patient, the four most important complaints from the patients’ perspective. Physicians in the intervention group then decide, for every drug listed, whether the indication is correct, whether there are side effects, whether an alternative treatment would be suitable or whether a change in the dosage is indicated (key questions of the algorithm). After discussion with the patient, the PCP and patient decide together whether to stop a drug, to change the dosage of a drug or to switch to an alternative drug, with the option to restart if symptoms should increase or the disease deteriorate.

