### Secondary outcome measures

Table 1 displays the secondary outcomes with the appropriate measuring method.

**Table 1 Tab1:** Secondary outcomes and the appropriate measuring method

Secondary outcomes	Measuring method
1. Change in the number of drugs immediately after the encounter and 6 months later	Medication list at baseline and after 6 months
2. Reason for a change, categorized in the 4 options of the algorithm, number of drugs in each category 12 months after applying the tool	Medication list of the changed medications after the intervention, with the reason for a change
3. Discrepancy in the decision to quit, change or continue the drug between PCP and patient	Medication list after intervention with any suggestion from the PCP for a change; medication list after the intervention and after shared-decision-making
4. Number of drugs for which the patient is suggesting a change	Medication lists at baseline, after 6 and 12 months
5. Number of drugs the patient is taking not known to the PCP	Medication lists at baseline, after 6 and 12 months
6. Time consumption of the intervention	Measurement of the time through the practice nurse and the PCP
7. Disease-specific variables to evaluate the course of the disease(s) for which the patient is being treated	Symptom scores and measurements of biometric analysis (e.g. blood pressure monitoring, serum glucose) and VAS scales (e.g. pain). Event rates (hospitalization, death) and unexpected adverse event rates
8. Number of drugs readopted due to an unfavorable course of the disease(s) (readoption rate)	Medication lists at baseline, after 6 and 12 months
9. Quality of life (QoL)	Patient rating on a 5-point Likert scale
	EQ-5D-3 L at baseline, after 6 and 12 months
10. Barriers perceived by patients and PCPs against the approach/algorithm	Phone interview with the patients 13 months after intervention
11. Number of drugs which have been started	Medication lists at baseline, after 6 and 12 months

*EQ-5D-3 L* EuroQol health status measure, *PCP* primary care practitioner, *VAS* visual analogue scale

After the baseline assessment (including gender and living situation) systematic follow-up measurements will take place after 6 and 12 months.

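### Carrying the last drug count forward may bias the 12-month effect in an unknown direction and overstates precision, and the undefined per-protocol check may not isolate that effect

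*Protocol article*

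**What the plan says.** The primary outcome (Primary outcomes measures) is: "Change in the number of drugs (deprescribing rate) 12 months after applying the tool". It is computed from medication lists at baseline and at 12 months. In the Statistical analysis section, the intention-to-treat rule is that "all available data from all individuals will be analyzed according to treatment group assignment", and the primary outcome "will be compared by using a *t* test for independent groups comparison".

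The same section then fixes the handling of drop-outs: "The last observation carried forward (LOCF) method will be used for dealing with the missing data for patients who have dropped out". Two accompanying steps are named. The first is descriptive: "The drop-out rate and the causes of drop-outs will be compared between the two groups". The second is the check on the method: "To estimate the last observation carried forward-effect a per-protocol (PP) analysis will be applied". The per-protocol population is not defined.

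Two other places bear on whether a count can be assumed to stay fixed. The Intervention section has drugs stopped or changed "with the option to restart if symptoms should increase or the disease deteriorate". Table 1 lists readopted drugs and newly started drugs as secondary outcomes, and the text below it says that "systematic follow-up measurements will take place after 6 and 12 months".

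**The concern.** Carrying a value forward assumes that the patient's drug count does not change after the last list. The protocol's own outcomes assume that it does. Whether deprescribing lasts to 12 months is the trial's question, and for drop-outs this method supplies the answer by assumption.

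The value to be carried is also not fixed. A patient lost before month 6 could carry the baseline list, which sets the change to zero. In the intervention arm the patient could instead carry the list made after the shared decision, which treats every stop as permanent. Table 1 includes a count taken right after the consultation among the secondary outcomes, but the measuring method beside it names only the baseline and 6-month lists. The first choice tends to shrink the effect and the second can enlarge it.

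The check is the other difficulty. A useful sensitivity analysis keeps the question and varies the missing-data assumption. A per-protocol analysis ordinarily changes who is analysed. If it does so here, agreement with the main result would not show that carrying forward is harmless, and disagreement could not be attributed to it.

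**Working it through.** **Inputs from the protocol article (Sample size calculation).** SD 2.8, target difference 1 drug, ICC 0.02, 30 clusters of 13 (195 per arm), drop-out 10%, 215 patients per arm. The inflation reproduces as a multiplication: 30 × 1.10 = 33 physicians and 195 × 1.10 = 214.5, or 215 per arm.

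**Assumed, because the document does not give them.** When patients drop out, which list is carried, and how counts develop over the year.

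**Bias.** For each arm, let d be the drop-out share, L the mean carried change among drop-outs and M their true mean 12-month change. Then

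bias = d₁(L₁ − M₁) − d₀(L₀ − M₀), with 1 = intervention and 0 = control.

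In all rows but the last, the true effect is −1.00 and the control change is zero.

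| Scenario | Bias | Expected estimate |
|---|---|---|
| 10% each arm, all carry baseline | 0.10 × (0 + 1) = +0.10 | −0.90 |
| 10%, half carry baseline, half an unchanged 6-month value | 0.10 × (−0.5 + 1) = +0.05 | −0.95 |
| 10%, 6-month value carried, effect constant | 0.10 × (−1 + 1) = 0 | −1.00 |
| 10%, 6-month value carried, effect wanes from −1.5 to −1 | 0.10 × (−1.5 + 1) = −0.05 | −1.05 |
| 10%, post-encounter list carried, drop of 2 drugs, half later reversed | 0.10 × (−2 + 1) = −0.10 | −1.10 |
| 20% each arm, all carry baseline | 0.20 × (0 + 1) = +0.20 | −0.80 |
| No true effect, both arms drift +0.5, drop-out 15% v 5%, baseline carried | 0.15 × (−0.5) − 0.05 × (−0.5) = −0.05 | −0.05 |

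A simulation of every row except the post-encounter one agrees to within 0.01. It used 4,000 replicates, 15 clusters of 13 per arm, drop-out completely at random, a 6-month SD of 0.75 times the 12-month SD and a 6/12-month correlation of 0.6. None of these scenarios has drop-out that depends on the unseen outcome.

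**Precision, baseline carried, 10% drop-out, clustering ignored.**

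- Carried forward: SD ≈ √(0.9 × 2.8²) = 2.66 and n = 215 per arm, so SE = 2.66 × √(2/215) = 0.256.
- Observed 12-month counts only: SD 2.8 and n = 0.9 × 215 = 193.5 per arm, so SE = 2.8 × √(2/193.5) = 0.285.
- Ratio: 0.256/0.285 = 0.90.
- Test statistics: −0.90/0.256 = −3.52 and −1.00/0.285 = −3.51.

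The interval is narrower, but the estimate has shrunk in the same proportion. A bias of 0.10 is 0.10/0.285, about 0.35 of a standard error.

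**Is the carried-forward SE wrong for its own estimator?** In the simulation (195 per arm) with ICC 0, the nominal SE is 0.270 and the empirical SE 0.268, so they agree. With ICC 0.02 they are 0.269 and 0.299. That gap comes from a t test that ignores clusters, not from carrying values forward. Across the 10% drop-out scenarios with a true effect, the nominal SE is 0.27 to 0.28, against 0.30 from observed 12-month counts, which is 7 to 10% smaller.

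**The case against.** A reader might infer that the effect estimate is certainly biased, that its standard error is wrong and that the per-protocol analysis is plainly misused. The documents do not support any of these.

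- **Bias.** Its sign and size depend on drop-out timing and trajectories that the protocol does not state. It is nil if mean counts are flat after the last list. The +0.10 row needs every drop-out to carry baseline, the −0.10 row rests on assumed figures, and 20% is twice the planned rate. This stands, so the claim is a possible bias of unknown direction.
- **Standard error.** The 10% gap compares two different estimators. It does not show an error in the SE of the carried-forward mean, and the test statistic barely moves when baseline is carried. This stands too. The point on precision is limited: filled values are treated as observed 12-month data, so the interval for the 12-month effect looks tighter than the observed counts justify.
- **Per-protocol set.** It appears in the drop-out paragraph with the stated purpose of gauging the carry-forward effect, so it may mean patients with complete follow-up. That would be close to a complete-case analysis. The criticism bites only if non-adherent patients are excluded, and the article does not say.
- **Drop-out comparison.** Comparing drop-out rates and causes between arms is planned and helps to reveal differential loss. It describes drop-out, however, and does not vary the assumption about the missing counts.

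A mixed model is not assumption-free either. A patient lost before month 6 has only a baseline count, so the model relies on missing at random, which cannot be tested. It also implicitly assigns 12-month counts to patients who died.

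**Conclusion.** The concern holds in a limited form. The plan commits to carrying counts forward as its only method for drop-outs, although its own outcomes expect those counts to move. The 12-month effect may be biased in either direction, by roughly 0.1 drug or less on a 1-drug target at 10% drop-out. That size rests on the assumed timings and trajectories tabulated above and on drop-out unrelated to the unseen outcome. Larger or unequal drop-out could change it. Precision is overstated only in the sense that filled values pass as observed ones.

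The per-protocol set is undefined. If it removes patients for non-adherence, it combines the effects of carrying forward, adherence and selection and cannot isolate the first. As written, no stated analysis clearly varies the missing-data assumption. This is worth correcting before analysis because the correction is cheap. It does not by itself put the trial's conclusion in doubt.

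**What to change.** - **Primary analysis.** Use a linear mixed model on the observed counts at baseline, 6 and 12 months, with practice and patient random effects, the 12-month between-arm contrast as primary and no single imputation. Because the outcome is a change, let the practice effect act on change from baseline as well as on level. State that the model is valid under missing at random, and state how deaths are handled.
- **Sensitivity analyses.** Keep last observation carried forward here, and specify which list is carried. Replace the per-protocol sentence with a complete-case analysis and a delta-adjusted analysis that allows data to be missing not at random.
- **Per-protocol.** Define the population, and keep the analysis only as a separate look at adherence.

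No new data are needed, since all three counts are already collected and the plan already foresees hierarchical regression. The cost is revised text and code, slightly more analysis work and possibly a slightly wider interval.
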